## Abstract

**Background:**

Managing patients with polypharmacy is a challenging issue in primary care. The aim of this study is to determine whether a patient-centered systematic review leads to more appropriate medication use in patients without negatively affecting quality of life and the course of the disease.

**Methods/Design:**

The trial is a two-armed, double blinded cluster-randomized controlled trial. Primary care physicians (PCPs) will be randomly assigned to the intervention or control group. Physicians in the intervention group undergo training with instruction of the algorithm. The control group is given a lecture on multimorbidity and instructions for collecting data in a usual care manner.

PCPs will approach patients aged 60 years or older who are taking 5 or more drugs. The study period is 1 year.

The primary outcome measure is the change in the number of drugs 12 months after the algorithm was applied by the PCP during consultation with the patient. Secondary outcomes are: change in the number of drugs immediately after the encounter and 6 months later, reason for a change of the medication, discrepancy in the decision to change between PCP and patient, number of drugs for which the patient is suggesting a change, number of drugs the patient is taking that are not known to the PCP, time consumption of the intervention, disease-specific variables to evaluate the course of the disease(s) for which the patient is being treated , quality of life, barriers against using the algorithm, numbers of drugs readopted due to an unfavorable course of the disease, and numbers of drugs which have been started.

**Discussion:**

Answering the four questions of the algorithm requires a weighing-up of risks and benefits and contains a shared-decision-making approach: a prioritization of the treatment goals is necessary. This can only be done in collaboration with the patient. The majority of patients with multimorbidity are treated in the primary care setting. This underlines the significance of our study carried out in this setting: given the high prevalence of adverse drug events in patients with multimorbidity an intervention like ours has a large potential to reduce drug-related morbidity.

**Trial registration:**

ISRCTN16560559 13 November 2014

## Background

The intake of multiple drugs (polypharmacy), overuse and misuse of drugs are increasing problems in the care of people with a number of health conditions (multimorbid) as well as older people [1, 2]. One of the problems in polypharmacy is the danger of adverse drug reactions [3]. This leads to an increase in morbidity, hospital admissions [4, 5], health-related costs [6] and number of deaths [7, 8]. Paradoxically, a clear relationship between polypharmacy and underuse of indicated drugs has been shown [9–11]. Up to now, several clinical tools and approaches to guide appropriate prescribing of drugs are available [11-14]. Deprescribing is a complex process that is required for the safe and effective cessation of inappropriate medications [3]. Barriers to and enablers of deprescribing from the point of view of the patients as well as from primary care physicians (PCPs) have been investigated [3, 15–18]. A recently published study using a newly developed algorithm for a systematic reduction of medication (Good Palliative Geriatric Practice, GPGP) showed that deprescribing resulted in a significant positive effect on health in older patients [19, 20]. In our study, we slightly adapted the GPGP algorithm and pilot-tested the algorithm in a primary care setting to assess feasibility and practicability [21]. The algorithm enforces a systematic drug review considering patients’ perspective and preferences. As primary care physicians (PCPs) take care of the majority of patients with multimorbidity, our tool has a potentially high impact on polypharmacy in primary care settings. Previous studies, investigating interventions to reduce polypharmacy, have taken place in an older persons care setting. In primary care settings results are still lacking. This study intends to bridge this gap.

### Study hypothesis

The implementation of an algorithm adapted to the GPGP leads to a reduction of polypharmacy among patients with multimorbidity (60 years and older) in a primary care setting.

Furthermore, this implementation does not worsen the quality of life or the course of the disease for which the drug was originally prescribed for (safety issues of the intervention).

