### Secondary outcome measures

Table 1 displays the secondary outcomes with the appropriate measuring method.

**Table 1 Tab1:** Secondary outcomes and the appropriate measuring method

Secondary outcomes	Measuring method
1. Change in the number of drugs immediately after the encounter and 6 months later	Medication list at baseline and after 6 months
2. Reason for a change, categorized in the 4 options of the algorithm, number of drugs in each category 12 months after applying the tool	Medication list of the changed medications after the intervention, with the reason for a change
3. Discrepancy in the decision to quit, change or continue the drug between PCP and patient	Medication list after intervention with any suggestion from the PCP for a change; medication list after the intervention and after shared-decision-making
4. Number of drugs for which the patient is suggesting a change	Medication lists at baseline, after 6 and 12 months
5. Number of drugs the patient is taking not known to the PCP	Medication lists at baseline, after 6 and 12 months
6. Time consumption of the intervention	Measurement of the time through the practice nurse and the PCP
7. Disease-specific variables to evaluate the course of the disease(s) for which the patient is being treated	Symptom scores and measurements of biometric analysis (e.g. blood pressure monitoring, serum glucose) and VAS scales (e.g. pain). Event rates (hospitalization, death) and unexpected adverse event rates
8. Number of drugs readopted due to an unfavorable course of the disease(s) (readoption rate)	Medication lists at baseline, after 6 and 12 months
9. Quality of life (QoL)	Patient rating on a 5-point Likert scale
	EQ-5D-3 L at baseline, after 6 and 12 months
10. Barriers perceived by patients and PCPs against the approach/algorithm	Phone interview with the patients 13 months after intervention
11. Number of drugs which have been started	Medication lists at baseline, after 6 and 12 months

*EQ-5D-3 L* EuroQol health status measure, *PCP* primary care practitioner, *VAS* visual analogue scale

After the baseline assessment (including gender and living situation) systematic follow-up measurements will take place after 6 and 12 months.

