### Statistical analysis

The primary data analysis will follow the intent-to-treat (ITT) approach. This means that all available data from all individuals will be analyzed according to treatment group assignment, regardless of whether or not each individual actually received the assigned treatment.

The primary outcome, change in the number of drugs 12 months after applying the deprescribing tool, will be compared by using a *t* test for independent groups comparison. Hierarchical regression will be used to consider the cluster-design for potential confounder. Determinants associated with a change of the medication are investigated by exploratory, multivariate regression analysis.

For secondary outcomes, parametric (*t* test) or non-parametric tests (chi-square and Wilcoxon test) will be used where appropriate.

Descriptive statistics will be used to describe the study population. Drop-out and loss to follow-up will be described.

In case of study discontinuation the collected data that are hitherto available will be anonymized and evaluated.

The last observation carried forward (LOCF) method will be used for dealing with the missing data for patients who have dropped out. The drop-out rate and the causes of drop-outs will be compared between the two groups to investigate the possible influence of the intervention. To estimate the last observation carried forward-effect a per-protocol (PP) analysis will be applied.

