## Discussion

The aim of this study is to determine whether a systematic review with a specific algorithm leads to more appropriate medication use in patients with multimorbidity (60 years and older) without worsening their quality of life and the course of the disease. Up to now, similar interventions have been tested in older populations but not in a primary care setting. In this setting, it is crucial, that an intervention is time-saving for enabling implementation in the daily clinical practice. In the pilot study the expenditure of time was 15 minutes (median; interquartile range (IQR): 10–30). The feasibility and acceptability was rated with a 5-point Likert scale in different items (means: 3.2–4.2, SD 0.83–1.3). Other studies concerning improving appropriate prescription in (mostly older) patients receiving complex polypharmacy present a more time-consuming algorithm or method than usual care [26]. The time aspect might be a strength of our approach in comparison to other ongoing studies [14, 15, 24].

A special feature of our study is the investigation of overtreatment as well as undertreatment. After piloting the study, an extension was made: beside the list of medications in use a special section was added with “medication started.”

Prioritization of patient’s problems is a crucial issue in the shared-decision-making process. To foster this approach and discussions between physician and patient on this issue, we added a list of the four most important complaints from the patient’s perspective to our tool in in parallel with the list of the four major clinical problems defined by the PCP.

Based on other studies [24], measurements of EQ-5D-3 L might even enable an economic evaluation of the danger of adverse drug reactions.

Finally, our study contains an exploratory part, as patient’s barriers and enablers against the approach will be inquired systematically 13 months after intervention. This has the potential to optimize the algorithm or further adapt it to the specific needs of primary care.

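### The no-worsening hypothesis for quality of life and disease course is paired only with difference tests, and no margin or confidence-interval criterion is stated

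*Protocol article*

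**What the plan says.** The Study hypothesis section has two parts. The first concerns a reduction in polypharmacy. The second is that "this implementation does not worsen the quality of life or the course of the disease for which the drug was originally prescribed", which the article labels the safety side of the intervention. The abstract gives the aim as finding out whether the review "leads to more appropriate medication use in patients without negatively affecting quality of life and the course of the disease", and the Discussion repeats "without worsening their quality of life and the course of the disease".

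Table 1 lists both concepts among the secondary outcomes. Item 7 is "Disease-specific variables to evaluate the course of the disease(s) for which the patient is being treated". Item 9 is quality of life, measured by a five-point Likert rating and by "EQ-5D-3 L at baseline, after 6 and 12 months".

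For secondary outcomes, the Statistical analysis section names a t test "or non-parametric tests (chi-square and Wilcoxon test) will be used where appropriate". The article gives no non-inferiority margin, equivalence test or confidence-interval criterion for either outcome. The Sample size calculation rests on the number of drugs alone.

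**The concern.** A claim that something does not get worse is a non-inferiority claim. Supporting it means ruling out a deficit of some stated size. The tests named start from the null hypothesis of no difference and can only reject it. When they fail to reject, the reason may be that there is no harm, or that the data are too few or too noisy to show it.

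With no other criterion in the text, half of the study hypothesis, the half about patient safety, has no stated analysis that could confirm it. Any later statement that deprescribing left quality of life and disease course intact would be easiest to make where the information is weakest. This goes beyond missing detail: the article states a hypothesis and assigns it a family of tests that cannot support it.

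**Working it through.** **Inputs from the Sample size calculation:** 30 clusters of 13 patients, so 390 in total and 195 per arm; two-sided alpha 0.05; ICC 0.02, stated for the primary outcome; SD 2.8 drugs; difference of 1 drug; power 80%.

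**Not in the article, hence assumed:** an SD, ICC and margin for quality of life. Results are therefore in SD units, and the ICC is varied over 0, 0.02 and 0.05.

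**The plan's own figure (number of drugs).**
- Design effect = 1 + (13 − 1) × 0.02 = 1.24.
- Effective n per arm = 195 / 1.24 = 157.3.
- SE = 2.8 × √(2/157.3) = 0.316.
- Power = Φ(1/0.316 − 1.96) = about 89%, or about 86% with a t reference on 28 degrees of freedom.

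The stated 80% is not reproduced; the planned size is conservative for its own inputs. That is a separate matter, and nothing below depends on it. The article gives no power or precision figure for quality of life.

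**Precision for a quality-of-life score.** SE = √(2 / effective n) in SD units, and half-width = 1.96 × SE.

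| ICC | Effective n per arm | SE | 95% CI half-width |
|---|---|---|---|
| 0 | 195.0 | 0.101 | 0.20 |
| 0.02 | 157.3 | 0.113 | 0.22 |
| 0.05 | 121.9 | 0.128 | 0.25 |

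At ICC 0.02, an observed difference of zero leaves a deficit of up to 0.22 SD not excluded. An estimate at the edge of non-significance, the extreme case, leaves up to 0.22 + 0.22 = 0.44 SD.

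**Chance that a true worsening d is non-significant.** Φ(1.96 − d/SE) − Φ(−1.96 − d/SE).

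| True worsening | ICC 0 | ICC 0.02 | ICC 0.05 |
|---|---|---|---|
| 0.1 SD | 83% | 86% | 88% |
| 0.2 SD | 49% | 57% | 66% |
| 0.3 SD | 16% | 24% | 35% |

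**Power of a non-inferiority reading if there is truly no difference.** Φ(margin/SE − 1.96).

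| Margin | ICC 0 | ICC 0.02 | ICC 0.05 |
|---|---|---|---|
| 0.20 SD | 51% | 43% | 35% |
| 0.30 SD | 84% | 76% | 65% |
| 0.35 SD | 93% | 87% | 78% |

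For example, at ICC 0.02 and a margin of 0.35 SD: 0.35/0.1128 − 1.96 = 1.14, and Φ(1.14) = 0.87. The margin that gives 80% power is (1.96 + 0.84) × SE, which is 0.32 SD at ICC 0.02 (0.28 at ICC 0, 0.36 at ICC 0.05).

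The last three tables use the normal approximation. With 30 clusters, a t reference on 28 degrees of freedom (critical value 2.05) widens the ICC 0.02 half-width slightly, to 2.05 × 0.113 = 0.23 SD.

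**The case against.** The strongest reply is that nothing presents this as a formal non-inferiority trial. The primary outcome and the sample size concern the number of drugs, the no-worsening statement is labelled a safety matter, and both measures are secondary. A journal article may also leave a margin for a secondary safety outcome to an analysis plan that is not shown here. This stands in part: a missing margin would not by itself be a finding. It does not remove the mismatch, because the statement sits under the study hypothesis, recurs twice as part of the aim, and is given tests that cannot support it.

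The article also describes other safety evidence. Adverse events go to a safety board that judges any link with the intervention, physicians in both groups rate the course of the main diseases, and readopted drugs are counted. This is useful, and the safety picture would not rest on a quality-of-life test alone. But case-by-case causality review is not a between-arm comparison, and the other measures fall under the same difference tests.

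Two stronger readings are tempting, and the document supports neither:

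- A reader might infer that the plan will treat p > 0.05 as proof of no harm. No section says so, none gives any decision rule for this hypothesis, and nothing rules out reporting estimates with intervals.
- A reader might infer that last observation carried forward will pull the arms together and favour a no-harm result. The direction depends on who drops out, when and why, and the article does not show it. The article also compares drop-out rates and causes between groups and adds a per-protocol analysis to gauge the effect of that method.

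**Conclusion.** The concern holds in a limited form: the stated analysis cannot establish the stated no-worsening hypothesis, and the article gives no margin or interval criterion that could. It should be fixed, but it leaves the primary analysis, the sample size and the data collection untouched.

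The size depends on what counts as a relevant harm, which the article does not say. If 0.2 SD matters, the planned trial would return a non-significant test roughly half to two thirds of the time despite that harm. If only 0.3 SD matters, the figure is roughly one in six to one in three. These ranges assume 195 evaluable patients per arm and an ICC for quality of life between 0 and 0.05; the 0.02 in the article belongs to the primary outcome.

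**What to change.** - **Quality of life.** Name EQ-5D-3L at 12 months as the measure on which the claim is judged. State a margin and its justification before any unblinded outcome data are seen. Conclude no worsening only if the cluster-adjusted two-sided 95% confidence interval for intervention minus control excludes a deficit as large as the margin. Otherwise report the largest deficit not excluded.
- **If no margin can be justified.** Reword the second hypothesis, and the matching sentences in the abstract and Discussion, as descriptive estimation of safety with confidence intervals.
- **Disease-course measures.** Report cluster-adjusted confidence intervals and the largest harm not excluded, and draw no not-worse conclusion from p > 0.05.

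The cost is text only, with no extra patients or measurements. The downside is that the no-harm claim becomes harder to make. At ICC 0.02 and no true difference, the planned size gives about 76% power for a margin of 0.30 SD and 87% for 0.35 SD. A margin of 0.20 SD would need about 488 evaluable patients per arm for 80% power (393 per arm without clustering × 1.24), far above the 195 planned. The 0.30 and 0.35 SD figures illustrate feasibility and are not recommended margins; the margin has to be justified on what loss of quality of life would matter to patients.

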## Methods/Design

We will conduct a cluster-randomized controlled trial (randomization on PCP-practice level) with primary care physicians in the northern part of Switzerland (see Fig. 1). The design and methodology of our study is based on the experiences of a small pilot study.

**Fig. 1 Fig1:**
[figure not shown]
Study flow chart

### Pilot study

The pilot study [21] was conducted with 14 primary care physicians. An evaluation was conducted to test the logistics, baseline measurements and the feasibility of the study. The pilot study resulted in minor changes in the questionnaire and an important element of shared-decision-making was added: beside the four major clinical problems defined by the PCP the four most important complaints in a patient’s perspective were added. In order to detect potential undertreatment a special section was added entitled “medication started”. 

### Recruitment and eligibility of primary care physicians

PCPs are eligible for participation if they provide care in the routine primary setting to unselected patients. About 1700 PCPs in the Canton of Zurich will be invited by a formal letter of the Institute of Primary Care of the University of Zurich.

PCPs who finally agree to participate will be listed in alphabetical order. If two PCPs of the same practice agree to participate, the first name in the alphabet receives a number which is valid also for the second one in order to avoid contamination between groups. Randomization will be stratified according to the practice size (e.g. single-handed versus group practice). The randomization scheme will be generated by using the website Randomization.com (http://www.randomization.com) and group assignment will be performed by a study nurse not involved in further data analysis. The PCPs with the corresponding numbers will be randomly allocated to the intervention and control group, respectively.

PCPs will be informed only after completion of the study about the group they have been randomized to (intervention or control group) in a debriefing session. At this time, an education session on how to use the algorithm will be offered to the control group.

If the number of the required 33 (see power calculation below) participating PCPs cannot be reached, the randomization will be done with the interested PCPs and the recruiting will be expanded to other Cantons of the northern area of Switzerland, followed by another randomization process.

Each PCP in the intervention and control groups will receive a financial allowance.

### Patient recruitment

All PCPs are asked to approach, consecutively and regardless of the reason for the current consultation, patients aged 60 or older who are taking 5 or more long-term drugs.

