### Intervention

Blinding of PCPs is not possible in this study design and even participation in a study addressing a certain topic can influence a physician’s behavior. To achieve a degree of blinding, PCPs are not provided with specific information at invitation. They will receive a lecture (length: 2 hours) about multimorbidity in general and instructions for collecting data in a usual care group. PCPs from the control group will be told that the study purpose is to investigate best practices for physician-patient communication.

PCPs in the intervention group will undergo a physicians’ training with instruction on how to use the algorithm including a communication skills training. The adapted GPGP-algorithm used in our trial consists of four steps and is a patient-centered process. First, the drugs are listed together with the four main diagnoses as well as the four main disorders from the patient’s perspective. Then the following steps will be systematically followed (see Fig. 2):

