**Fig. 2 Fig2:**
[figure not shown]
Improving drug therapy in primary care (adapted from [20] and [21])

Indication of the drug in this patient (identifying undertreatment or overtreatment)Do the known possible adverse reactions of the drug outweigh the possible benefits? (Potential adverse events)Can the dosing rate be reduced with no significant risk? (Dosing problems)Is there another drug that may be superior to the one in question?

Finally, the result of this analysis will be discussed together with the patient. For each drug the PCP will note whether the patient agrees with the recommendation.

After obtaining informed consent from the patient, a practice nurse or the PCP creates a list of the patient’s present medication. Then, the PCP defines the four major clinical problems and, together with the patient, the four most important complaints from the patients’ perspective. Physicians in the intervention group then decide, for every drug listed, whether the indication is correct, whether there are side effects, whether an alternative treatment would be suitable or whether a change in the dosage is indicated (key questions of the algorithm). After discussion with the patient, the PCP and patient decide together whether to stop a drug, to change the dosage of a drug or to switch to an alternative drug, with the option to restart if symptoms should increase or the disease deteriorate.

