### Timeframe of the study

The recruitment of the PCP is planned over 2 months between March and May 2015.

Patients’ eligibility screening and patient inclusion is projected within a period of 4 months. The aim is to include 1 patient/week per PCP.

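### The abstract's double-blind label contradicts the Intervention section, and patients are recruited after allocation by physicians who know the intervention they deliver

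*Protocol article*

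**What the plan says.** On blinding, the abstract (Methods/Design) states: "The trial is a two-armed, double blinded cluster-randomized controlled trial". The Intervention section states: "Blinding of PCPs is not possible in this study design". It then describes a limited substitute: "To achieve a degree of blinding, PCPs are not provided with specific information at invitation". Control physicians are also told that the study concerns physician-patient communication. The section on recruitment of primary care physicians (PCPs) adds that "PCPs will be informed only after completion of the study about the group they have been randomized to", at a debriefing.

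On training, the Intervention section says "PCPs in the intervention group will undergo a physicians’ training with instruction on how to use the algorithm including a communication skills training".

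On patient entry, the Patient recruitment section says "All PCPs are asked to approach, consecutively and regardless of the reason for the current consultation, patients aged 60 or older", provided they take five or more long-term drugs. The Timeframe section adds "The aim is to include 1 patient/week per PCP", over four months. PCPs give patients the study information (Patient informed consent). The text under Fig. 2 continues: "After obtaining informed consent from the patient, a practice nurse or the PCP creates a list of the patient’s present medication". Intervention PCPs then put the algorithm's questions to each listed drug.

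On the outcome, the change in drug count is taken from medication lists supplied by the practice nurse or the PCP at baseline and 12 months (Primary outcomes measures).

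**The concern.** There are two linked problems. The first is factual: the article claims a property that its own Intervention section denies. A reader who trusts the abstract would assume that neither recruitment nor outcome recording could be influenced by knowledge of the arm.

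The second is the risk that the label hides. Randomising practices balances practices. It does not balance patients who are identified, approached and asked for consent afterwards by people who know what they have been trained to do. A PCP trained to look for drugs that could be stopped may, without intending it, more readily approach patients who seem to have such drugs, or explain the study to them differently. A control PCP told that the study is about communication has no such prompt. If entry differs by arm, the difference in 12-month change mixes the effect of the algorithm with a difference in who was enrolled. The practice that recruits also writes the list from which the primary outcome is counted, so knowledge of the intervention is present at both ends.

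**Working it through.** **Step 1: the label.** The abstract says double blinded. The Intervention section says PCPs cannot be blinded and that only a degree of blinding is sought. Withholding the group name until debriefing does not reconcile the two: an intervention PCP attends algorithm training and then applies the algorithm drug by drug, so that PCP knows what is being delivered whether or not the arm has been named.

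**Step 2: the order of events.** PCPs agree to take part and are randomised. They then approach patients, inform them and obtain consent; the medication list follows; the intervention PCP then applies the algorithm. No single sentence says that training precedes the first approach to a patient. It is inferred: the described flow runs from consent through the list to the algorithm, and an untrained PCP could not complete it. The article describes no step in which patients are identified before allocation or by someone unaware of the arm.

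**Step 3: does the recruitment pace force selection?** Four months is 4 × 52/12 = 17.3 weeks. One inclusion a week gives about 17 patients per PCP, against 13 needed (Sample size calculation). The pace is compatible with the target and is worded as an aim for inclusions, not as a limit on approaches.

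**Step 4: the standard error implied by the plan.** Inputs, all from Sample size calculation: SD 2.8, ICC 0.02, 30 clusters of 13, difference of 1 drug, two-sided 5%.

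- Patients per arm: 15 × 13 = 195.
- Design effect: 1 + (13 − 1) × 0.02 = 1.24.
- SE of the difference: 2.8 × √(2 × 1.24/195) = 0.316 drug.
- Power for 1 drug: Φ(1/0.316 − 1.96) = 88.6% (86.4% using a t distribution with 28 df).

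The plan states 80%, so its figure does not reproduce from its own inputs. The difference is on the safe side and is a separate matter; the illustration below uses the inputs, not the stated power.

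**Step 5: illustration of sensitivity.** Suppose the algorithm has no effect but recruitment shifts the between-arm difference in mean change by *b*. The chance of a significant result is 1 − Φ(1.96 − b/SE) + Φ(−1.96 − b/SE).

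| Assumed shift *b* (drugs) | b/SE | Two-sided type I error |
|---|---|---|
| 0 | 0 | 5.0% |
| 0.1 | 0.32 | 6.2% |
| 0.25 | 0.79 | 12.4% |
| 0.5 | 1.58 | 35.3% |

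The values of *b* are assumptions; nothing in the documents supports one over another. The calculation also assumes a test whose standard error allows for clustering.

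**The case against.** The article contains real safeguards. Approach is to be consecutive and independent of the reason for the visit, which on paper leaves PCPs no choice. Little is disclosed at invitation, the group name is withheld until debriefing, and control PCPs are given another study purpose, so they have little reason to select on drugs that could be stopped. All of this stands and lowers the risk. It does not remove it: the person asked to approach consecutively is the person trained in the algorithm, and that person also informs the patient.

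A reader might go further and infer that consecutive approach and one patient a week contradict each other, so that PCPs must pass over most eligible patients. Assuming 2 to 10 eligible attenders a week, that reading would put the share passed over at 50% (1 − 1/2) to 90% (1 − 1/10). The documents do not support it. The weekly figure is an aim for inclusions; no sentence tells a PCP to stop after one patient, refusals would slow inclusion, and the number of eligible attenders is not given. The article simply does not say how the two instructions work together.

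Nor can it be inferred that there is no screening log or detailed recruitment instruction. The article condenses a fuller protocol that is not shown, and such detail is commonly left to it.

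**Conclusion.** The contradiction over blinding is certain and needs correcting. The recruitment risk is real but partly mitigated: PCPs recruit after randomisation and, by inference, after training, while knowing the intervention they deliver, and the stated safeguards lessen the risk without removing it.

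Neither the size nor the direction of any bias can be derived from the documents. A reader might infer that the effect will be inflated by some definite fraction of the 1-drug target; that would need assumptions about how often selection occurs and how many of the extra drugs stay stopped at 12 months, and the article gives no figure for either. What can be said is that the design is sensitive: with an implied SE of 0.316, an assumed shift of 0.1 to 0.5 drug would take the type I error from 5% to about 6% to 35%. The point should be acted on, but it does not show that the trial is biased.

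**What to change.** 1. Replace the double-blind label with a true description: PCPs are not blinded to the intervention they deliver, they are not told the name of their group until debriefing, and control PCPs are given a different study purpose.

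2. Take discretion out of the order of approach. Where practice records allow, draw up a coded list of eligible patients before training and have the study centre set the invitation order. Otherwise use a mechanical rule, such as the first eligible attenders from a set day each week. The second option is likely to be the more practical, since the article describes paper data collection and says nothing about searchable records. State how the rule fits the aim of one patient a week.

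3. Report the numbers eligible, approached and refusing, and baseline drug counts, by arm. Similar baseline counts would be reassuring but would not show that the drugs were equally easy to stop.

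Coding the drug counts by staff unaware of the arm would add little, because the list itself is written by the unblinded practice.

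The cost is a short amendment, a little practice time and a possible small delay. Trial status says patient recruitment had not started at first submission. If patients have since been enrolled, item 1 remains possible, and item 3 as far as the numbers were recorded.
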